## Abstract

**Background:**

The World Health Organization recommends that a woman waits at least 24 months after a live birth before getting pregnant again; however, an estimated 25% of birth intervals in low-income countries do not meet this recommendation for adequate birth spacing, and the unmet need for postpartum family planning (PPFP) services is high. Few randomized controlled trials have assessed the causal impact of access to PPFP services, and even fewer evaluations have investigated how such interventions may affect postpartum contraceptive use, birth spacing, and measures of health and well-being.

**Objective:**

This protocol paper aims to describe a randomized controlled trial that is being conducted to identify the causal impact of an intervention to improve access to PPFP services on contraceptive use, pregnancy, and birth spacing in urban Malawi. The causal effect of the intervention will be determined by comparing outcomes for respondents who are randomly assigned to an intervention arm against outcomes for respondents who are randomly assigned to a control arm.

**Methods:**

Married women aged 18-35 years who were either pregnant or had recently given birth were randomly assigned to either the intervention arm or control arm. Women assigned to the intervention arm received a package of services over a 2-year intervention period. Services included a brochure and up to 6 home visits from trained family planning counselors; free transportation to a high-quality family planning clinic; and financial reimbursement for family planning services, consultations, and referrals for services. Two follow-up surveys were conducted 1 and 2 years after the baseline survey.

**Results:**

A total of 2143 women were randomly assigned to either the intervention arm (n=1026) or the control arm (n=1117). Data collection for the first follow-up survey began in August 2017 and was completed in February 2018. A total of 1773 women, or 82.73% of women who were eligible for follow-up, were successfully contacted and reinterviewed at the first follow-up. Data collection for the second follow-up survey began in August 2018 and was completed in February 2019. A total of 1669 women, or 77.88% of women who were eligible for follow-up, were successfully contacted and reinterviewed at the second follow-up. The analysis of the primary outcomes is ongoing and is expected to be completed in 2021.

**Conclusions:**

The results of this trial seek to fill the current knowledge gaps in the effectiveness of family planning interventions on improving fertility and health outcomes. The findings also show that the benefits of improving access to family planning are likely to extend beyond the fertility and health domain by improving other measures of women’s well-being.

**Trial Registration:**

American Economics Association Registry Trial Number AEARCTR-0000697; https://www.socialscienceregistry.org/trials/697 Registry for International Development Impact Evaluations (RIDIE) Trial Number RIDIE-STUDY-ID-556784ed86956;
https://ridie.3ieimpact.org/index.php?r=search/detailView&id=320

**International Registered Report Identifier (IRRID):**

DERR1-10.2196/16697

## Introduction

### The Role of Family Planning

The World Health Organization (WHO) guidelines recommend that a woman wait at least 24 months after a live birth before getting pregnant again [1,2]. Poorly spaced births may contribute to higher rates of mortality for both mothers and infants [3,4]; however, an estimated 25% of birth intervals in low- and middle-income countries do not meet the WHO’s 24-month recommended guideline for adequate birth spacing [5]. This gap between recommended spacing and realized spacing highlights the importance of postpartum family planning (PPFP), particularly in sub-Saharan Africa where the unmet need for PPFP is high. Given that the ideal family size is higher among women in sub-Saharan Africa than in other parts of the world, the demand for and use of family planning is driven more from a desire to space future births rather than to limit births. Nevertheless, an estimated 8 million women in sub-Saharan Africa have an unmet need for limiting future births [6]. The continuing high unmet need for and lack of access to PPFP highlights the need to mobilize efforts toward meeting the family planning and fertility goals of postpartum women. To this end, interventions that aim to influence the demand and supply of PPFP have become increasingly common in developing countries. These interventions have targeted key populations in a variety of ways, from education and awareness programs in schools to multicomponent, community-based campaigns [7,8].

Recently, the number of family planning interventions that have undergone more rigorous impact evaluation has increased to assess the effects of family planning on fertility, health behavior, and health outcomes. However, findings from community-level social programs such as the Maternal and Child Health–Family Planning Extensions project in Matlab, Bangladesh, and the Navrongo experiment in Ghana have also shown that contraceptive use declines considerably following the discontinuation of family planning services [9-12]. Although not all the studies focused on postpartum women, these results suggest that increased access to high-quality family planning services, particularly for new mothers, needs to be expanded beyond the neonatal clinic. To this end, few randomized controlled trials have been conducted to assess the causal impact of family planning in low-income countries, and even fewer impact evaluations have been conducted to determine the extent to which such family planning interventions may affect downstream health and development outcomes. To date, not many impact evaluations have sought to identify the effectiveness of family planning and reproductive health programs at the individual or household level; apart from the frequently cited Matlab quasi-experimental study and a recent field experiment by Ashraf et al [13], no randomized controlled trial, to the best of our knowledge, has attempted to causally identify the impact of family planning and birth spacing on both immediate and longer-term outcomes of health and well-being in sub-Saharan Africa.

### Study Objectives

To address these gaps in the evidence, we conducted a randomized controlled trial to identify the causal impact of improved access to PPFP. The study population included married postpartum women aged 18 to 35 years in Lilongwe, Malawi. As part of the trial, each woman in the study was randomly assigned to either the treatment or control arm. A woman who was assigned to the intervention arm received a 2-year–long family planning intervention that was designed to reduce key barriers to access for postpartum women in urban Malawi [14,15]. The primary objective of this study is to evaluate the impact of the family planning intervention on contraceptive use, fertility, birth spacing, and other measures of maternal and child health and well-being in postpartum women who received the family planning intervention (the intervention arm) compared with women who did not receive the intervention (the control group). Primary outcomes include short-term outcomes related to modern contraceptive use and contraceptive method mix (the profile of the relative level of use of different contraceptive methods within our study sample) as well as intermediate outcomes related to fertility and birth spacing. Shorter-term secondary outcomes include changes in desired fertility, unmet need for family planning, and outcomes associated with maternal and child health, including safe pregnancy, birth height and weight, and nutritional status. Longer-term secondary outcomes include educational attainment (matriculation rates and years of schooling completed), labor market outcomes (employment status, female labor supply, and women’s time use), and income. This study seeks to fill the current knowledge gaps on the effectiveness of family planning interventions by directly identifying the impact of an increase in access to family planning on fertility and health outcomes. A downstream objective of this study is to demonstrate that the benefits of improving access to family planning are likely to extend beyond the health domain by also improving well-being and contributing to the alleviation of poverty.

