### Primary Outcomes

At the designated 1-year and 2-year follow-up periods, the entire study sample of women was resurveyed to create a panel of individual women in which each woman and household would be observed over 3 time periods. In each follow-up round, we collected survey data on a range of primary outcomes of interest, which include (1) contraceptive use, including changes in contraceptive prevalence, changes in method mix, and adherence to methods (compliance and discontinuation) and (2) fertility and birth spacing outcomes, including pregnancy status, parity, and time since the last birth.

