### Secondary Outcomes

A range of secondary outcomes were collected in each survey wave, including (1) child anthropometric outcomes, including child height, weight, and anemia status for all children born after the start of the intervention; (2) sexual and marital well-being; (3) women’s anthropometric outcomes, including height, weight, and anemia status; (4) women’s and children’s educational attainment, including time spent in school, type of school (public or private) attended, and the highest educational qualification achieved; (5) work, income, and women’s employment, including women’s time use (time spent on child care vs household and income-generating activities) and sources of household income; (6) household assets and wealth, including changes in asset ownership over time; and (7) expenditures, in particular changes in food expenditures and durable expenditures over time.

Outcomes were collected according to the schedule outlined in Table 2. All survey instruments (baseline and follow-up) and intervention-monitoring tools to track participants and intervention uptake over the course of the study are available upon request.

**Table 2 table2:** Outcome measures and instruments.

Outcomes and instruments	Baseline	Follow-up, year 1	Follow-up, year 2
Attitude and knowledge of family planning	✓^a^	✓	✓
Contraceptive use	✓	✓	✓
Pregnancy and fertility outcomes	✓	✓	✓
Child anthropometry (height, weight, and anemia)	—^b^	✓	✓
Women’s anthropometry (height, weight, and anemia)	✓	✓	✓
Educational attainment	✓	✓	✓
Formal and informal employment	✓	✓	✓
Women’s time use (primary and secondary activities)	✓	✓	✓
Household income and expenditure	✓	✓	✓
Household assets	✓	✓	✓
Baseline survey	✓	—	—
Year 1 follow-up survey	—	✓	—
Year 2 follow-up survey	—	—	✓

^a^✓: indicates that data on that outcome were collected in the indicated survey wave.

^b^–: indicates that data on that outcome were not collected in the indicated survey wave.

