### Analysis Plan

Analysis of quantitative study data will be conducted using STATA and R (the R Project), where appropriate. A descriptive analysis will be performed for all variables, and unadjusted comparisons between experimental arms will be conducted. Descriptive statistics will be performed, including frequencies, means, and standard deviations. In addition, chi-square tests and one-tailed *t* tests will be used to examine associations in the data. A *P* value <.05 will be considered statistically significant for all statistical tests that are conducted. Given our hypotheses of the impact of our intervention on our key outcomes, one-sided hypotheses tests will be conducted for all our main analyses. Continuous variables will be tested for normality and nonnormal values will be categorized or transformed appropriately.

Our main econometric specifications will estimate the intent-to-treat (ITT) effect of our family planning intervention on fertility and other outcomes by directly regressing our outcomes of interest on a binary variable indicating receipt of the intervention. The main econometric specification for estimating the ITT effect of our family planning intervention is defined as follows:

where *Y_it_* is the outcome variable of interest for woman *i* in the period *t*=0,1,2 for baseline, 1-year follow-up, and 2-year follow-up, respectively; *T_it_* is an indicator of assignment to the treatment arm; *X_it_* is a vector of individual-level covariates that are controlled for in the analysis; *_i_* is the individual-specific fixed effect; *Y_i0_* is the baseline level of the outcome; and *ε_it_* is the error term. Here, the outcome variables of interest include immediate, intermediate, and long-term outcomes mentioned in the previous sections.

We will conduct several subgroup analyses to examine how the family planning intervention effects vary across particular subpopulations. Subgroups of interest include pregnant women, new mothers, women who have previously used family planning, women who expressed a desire to space or limit births at baseline, poorer women, and women with low educational attainment. In addition, we will estimate heterogeneous treatment effects for girls, older children, and high-parity households.

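### The primary objective includes health and well-being measures that the outcome lists class as secondary, and a single .05 rule for all tests also covers the outcomes meant to show wider benefit

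*Protocol article*

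**What the plan says.** In Study Objectives, the primary objective is the effect on "contraceptive use, fertility, birth spacing, and other measures of maternal and child health and well-being in postpartum women". The next sentences of the same section narrow this: "Primary outcomes include short-term outcomes related to modern contraceptive use and contraceptive method mix", together with fertility and birth spacing. They then move health down a tier: "Shorter-term secondary outcomes include changes in desired fertility, unmet need for family planning, and outcomes associated with maternal and child health". The section closes on a further aim: "A downstream objective of this study is to demonstrate that the benefits of improving access to family planning are likely to extend" outside health, to well-being and poverty.

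The Methods follow the narrower version. Primary Outcomes has two groups, contraceptive use and "2) fertility and birth spacing outcomes, including pregnancy status, parity, and time since the last birth". Secondary Outcomes begins "A range of secondary outcomes were collected in each survey wave" and numbers seven domains. Sample Size and Power Calculations names two key outcomes, contraceptive prevalence and births per woman.

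The Analysis Plan sets one threshold: a P value below .05 "will be considered statistically significant for all statistical tests that are conducted". It makes the main analyses one-sided, and its main intent-to-treat model takes in the immediate, intermediate and long-term outcomes alike.

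**The concern.** Two stated features work against each other. First, one sentence makes the primary objective broader than the primary outcomes, so the text does not settle which results would meet it. Second, the wider-benefit aim is worded as something to be shown, while the outcomes that would show it are tested under the same .05 rule as the primaries, with no lower tier.

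What is at stake is the interpretation of secondary results. Asset, expenditure, schooling, employment and marital well-being measures each give a chance of a nominally significant result. Under the stated rule, one such result could be offered as evidence that access to family planning helps beyond health, at an error rate well above 5%.

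**Working it through.** **1. Status of health and well-being in each place**

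| Place in the protocol article | Status |
|---|---|
| Study Objectives, primary-objective sentence | included in the primary objective |
| Study Objectives, sentences that follow | maternal and child health, education, labor and income are secondary |
| Primary Outcomes | no health or well-being measure |
| Secondary Outcomes | anthropometry, sexual and marital well-being, education, work and income, assets, expenditures |
| Sample Size and Power Calculations | powered for contraceptive prevalence and births per woman only |

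The primary-objective sentence is out of line with the rest.

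**2. Alpha per outcome, checked against the plan's own power figures**

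Inputs: 730 women per arm; 19.5% against 26%; fertility SD 2; alpha .05.

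Proportions, continuity-corrected: power = Φ[(d − 1/n − z·se0)/se1].
- d = .065 and 1/n = 1/730 = .00137
- se0 = √(.2275 × .7725 × 2/730) = .02194
- se1 = √((.195 × .805 + .26 × .74)/730) = .02188
- One-sided, z = 1.645: Φ[(.06363 − .03610)/.02188] = Φ(1.26) = 0.896. Table 3 states 0.90.
- The other three rows give 0.794, 0.647 and 0.470, against 0.79, 0.65 and 0.47.
- Two-sided, the first row would be 0.827.

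Means: se = 2 × √(2/730) = .1047.
- 4.5 against 4.2: Φ(.3/.1047 − 1.645) = 0.889. Table 4 states 0.89.
- 4.5 against 4.3: 0.605. Table 4 states 0.61.
- Two-sided, these would be 0.818 and 0.480.

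So each powered outcome uses the full one-sided .05, with no split.

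**3. Which domains bear on the wider-benefit aim**

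That aim concerns benefit outside health. Of the seven secondary domains, (1) child and (3) women's anthropometry are physical-health measures. Five remain: sexual and marital well-being; education; work, income and employment; assets and wealth; expenditures.

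**4. Chance of at least one false positive**

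Assumptions, none of them stated in the protocol: one one-sided .05 test per domain, all null hypotheses true, and any single significant domain counted as support.

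Independent tests: 1 − (1 − .05)^k.
- k = 5: 1 − .95^5 = 22.6%
- k = 7: 1 − .95^7 = 30.2%

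Correlated tests were simulated with z_j = √ρ·u + √(1−ρ)·e_j, where u and e_j are independent standard normals. The rate is the share of 1,000,000 draws in which the largest z_j exceeds 1.645.

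| Correlation | 5 domains | 7 domains |
|---|---|---|
| 0 (exact) | 22.6% | 30.2% |
| 0.3 | 19.3% | 24.5% |
| 0.5 | 16.6% | 20.4% |
| 0.7 | 13.6% | 15.9% |
| 0.9 | 9.4% | 10.5% |

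More tests raise the rate. As an illustration only, two tests in each of five domains give 1 − .95^10 = 40.1% if all ten were independent. Measures of the same domain are unlikely to be independent, so the real figure for ten tests would be lower.

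**5. After adjustment**

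- Five domains at .05/5 = .010: 1 − .99^5 = 4.9%
- Seven domains at .05/7 = .0071: 4.9%

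Holm keeps the same 5% bound with more power than Bonferroni.

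**The case against.** The other side has real points.

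- **The ranking is settled nearly everywhere.** The sentences after the primary objective, both outcome sections, the power calculation and the Abstract's objective agree that health and well-being are not primary. A reader might infer that the protocol ranks them as primary in several places, so that a secondary success could be reported as meeting the primary objective. The documents do not support that: it is one sentence, and Secondary Outcomes already carries the right label. This stands, and reduces that half of the point to an alignment of wording.
- **No success rule is given.** A reader might infer that the plan has a built-in false-positive rate of 20–30%. It does not. That range needs one test per domain, any-one-counts, and all seven domains in the family, but the wider-benefit sentence covers only five. Counts such as one test per wave have no basis in the text either, which describes a panel specification. This stands, so every figure here is conditional.
- **A preanalysis plan is mentioned under Availability of Data and Materials but not shown.** It may adjust for multiple secondary outcomes, so the lack of an adjustment here is not itself a fault. But the article does more than stay silent: it states a .05 rule for every test. A plan that adjusts would need that sentence changed.
- **The verb may be loose introductory wording.** The Discussion speaks of investigating the extent of effects. Against that, the Abstract's Conclusions already present wider benefit as something the findings show, although the Results say the primary analysis is unfinished. The wording matters enough to correct.

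**Conclusion.** The point holds in a limited form. One sentence makes the primary objective wider than the primary outcomes and the power basis. Separately, the stated .05 rule for all tests, one-sided for the main analyses, sits beside an aim to show benefit outside health.

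If one significant domain were enough, with one test per domain and no true effects, the false-positive chance for the five relevant domains is 22.6% under independence, 16.6% at correlation 0.5 and 13.6% at 0.7. That is about 2.7 to 4.5 times the nominal 5% (13.6/5 and 22.6/5). Counting all seven domains gives 30.2% and 20.4% at correlations 0 and 0.5. Stronger correlation lowers these figures and several measures per domain raise them. The correlations are assumptions, because the document gives none.

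**What to change.** 1. In Study Objectives, limit the primary objective to contraceptive use, fertility and birth spacing, and state maternal and child health and well-being as secondary objectives.
2. In the Analysis Plan, restrict the unadjusted .05 rule to the primary outcomes. (Multiplicity among the primaries is a separate question, not addressed here.)
3. For the secondary domains, choose one route and state it:
   - If the wider-benefit claim is to stay confirmatory, report Holm or false-discovery-rate adjusted P values across domains, for example on one summary index per domain at Year 2, with the components descriptive. Holm bounds the chance of any false positive. False-discovery-rate control bounds the expected share of false claims and is the weaker guarantee.
   - Otherwise label these outcomes exploratory and replace the verb in the downstream objective with 'explore'.
4. If the preanalysis plan already does this, say so in the article and amend the .05 sentence to match.

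The cost is a few wording changes and routine computation, with no new data. Since the article reports the analysis as still under way, the change was feasible. The downside is that a single unadjusted secondary result can no longer be claimed as significant.

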## Methods

### Study Approval

Human subject approvals for this study were obtained from the Harvard University Institutional Review Board (IRB; Protocol Number: IRB16-0421), the Malawi National Health Sciences Research Committee (NHSRC Approval Number: 16/7/1628), the Lilongwe District Council, the Malawi Police Service, and the Malawi Ministry of Health (MOH) to conduct the study. Memoranda of Understanding were established with our partner family planning clinic in Lilongwe, the Good Health Kauma Clinic.

### Study Setting

Our study was conducted in urban Lilongwe, the capital of Malawi. Despite declining birth rates and improvements to maternal health care, the total fertility rate or the average number of births per woman has remained relatively high in Malawi. In 2017, the average total fertility rate in Malawi was 4.2 births per woman (with a slightly lower fertility rate in Lilongwe), which is below the average total fertility rate of 4.9 births per woman in sub-Saharan Africa, but almost twice the average total fertility rate of 2.7 births per woman in South Asia and more than twice the average total fertility rate of 2.2 births per woman in Latin America and the Caribbean [16,17]. In addition, estimates from the 2015-16 Malawi Demographics and Health Survey (MDHS) show that the contraceptive prevalence rate in Malawi was 45.2% among all women of reproductive age (15-49 years) and 59.2% among married women of reproductive age. These estimated contraceptive prevalence rates are a significant increase from the 32.6% and 46.1% prevalence rates for all women and married women, respectively, from the 2010 MDHS. Nevertheless, the unmet need for family planning has remained high, with an estimated 18.7% of women in Malawi reporting to have an unmet need for spacing or limiting births [17]. Injectable contraceptives were reported to be the most popular method in Malawi in 2010 and were used by 22.5% of women, followed by intrauterine devices (IUDs) and female sterilization at 9% and 8.3%, respectively [17]. The method mix of women has not changed significantly over time among married women in Malawi, as injectable contraceptives, IUDs, and female sterilization remain to be the most popular methods among married women and are used by 30%, 11.5%, and 10.9%, respectively [17].

When compared with antenatal care, the utilization of postpartum maternal health care services remains to be low in Malawi. Although 97.6% of pregnant women received antenatal care from a skilled professional between 2012 and 2017, 57.6% of new mothers did not receive any postnatal care within the immediate postpartum period (within 48 hours following birth) [17]. Although a range of maternal health programs have attempted to combine PPFP with existing maternal health services, these programs continue to face difficulties in reaching significant portions of the population. Prior studies have shown that women in Malawi and in sub-Saharan Africa more generally face a range of barriers to accessing high-quality postpartum care, including (1) informational barriers (lack of awareness or knowledge of postpartum care options), (2) physical barriers (distance to care, long travel times to health facilities, high cost of transport, and poor access to effective transport options), and (3) barriers that impede effective service provision (long waiting times at clinics, user fees for services, lack of availability of services and supplies, and poorly trained service providers, among others) [18]. Additionally, women and children often receive postnatal care from different locations and through different providers, which often compels a woman to make the choice to seek care for her child at the expense of her own care [19]. These barriers to access are common to interventions that aim to increase access to and use of postpartum health care services, including PPFP, and are key barriers that we aimed to address when designing our intervention.

